### Setting

The study is co-ordinated from the University Hospitals of Leicester. However, clinical measurement sessions and the educational programmes will be run in a variety of different locations within the Leicestershire area, including: hospital, primary care and community settings. Locations that are as near as possible to the recruited GP practices will be identified, including within the practice itself where possible.

### Treatment regimens

#### Control

Control subjects will receive a booklet detailing information on risk factors for type 2 diabetes and how physical activity and lifestyle change can be used to prevent or delay the disease. The leaflet addresses factors around type 2 diabetes risk using the five domains (causes, consequences, identity, control/treatment, and timeline) highlighted by Leventhal’s common sense model [27].

#### Intervention

The intervention group will be offered the Walking Away from Type 2 Diabetes group-based structured educational programme. This programme is based on the content and behaviour change techniques of the successful Prediabetes Risk Education and Physical Activity Recommendation and Encouragement (PREPARE) programme; a full description of the rationale, development and efficacy of which can be found elsewhere [9,28]. Walking Away will be delivered to 6–10 individuals by two trained educators over 3 hours and is primarily designed to promote walking activity by targeting perceptions and knowledge of impaired glucose tolerance and physical activity self-efficacy as well as promoting self-regulatory skills such as goal-setting strategies, self-monitoring, and relapse prevention (identifying and addressing barriers to change). Self-regulation is based around pedometer use, which has been demonstrated to be crucial to the success of the programme [9]. Specifically, those taking less than 6000 steps at baseline are encouraged to increase their activity levels by at least 3000 steps per day, equivalent to around 30 min of walking [29]. Those achieving more than 6000 steps per day are encouraged to try to reach at least 9000 steps per day, an amount that is likely to include 30 min of walking activity in addition to usual daily activity [29]. Those achieving more than 9000 steps per day are encouraged to at least maintain their current activity levels and informed that health benefits could be achieved by increasing their activity levels further. Goal attainment is encouraged through the use of proximal objectives. Participants are enabled to set an action plan detailing where, when and how their first proximal goal will be reached and encouraged to repeat this process for each new proximal goal. Participants are encouraged to wear their pedometer on a daily basis and to self-monitor their ambulatory activity using a steps-per-day log. Along with physical activity, the programme has a specific section dedicated to healthy dietary practices, particularly around the identification and substitution of food items high in saturated fat.

The programme content is underpinned by an integrated theoretical framework, focused on linking motivational and volitional determinants of health behaviour. The framework is based on mutually complementary health behaviour theories, including Bandura’s social cognitive theory [30], Gollwitzer’s implementation intentions [31], Leventhal’s common sense model [27], and Chaiken’s dual process theory [32] and was informed by, and modelled on, the person-centred philosophy and learning techniques developed for the DESMOND programme [13]; a nationally available self-management programme for those with type 2 diabetes run within half of all PCTs nationally. The programme was developed inline with the Medical Research Council’s Framework for Complex Interventions to Improve Health, which are internationally recognised criteria for guiding the development and evaluation of health behaviour change programmes [15,33].

The walking Away programme was adapted for a broader range of high risk individuals, such as those identified through a risk score, in order to make it suitable for translation into usual healthcare practice. This necessitated a shift in focus from the PREPARE programme, which targeted illness perceptions around prediabetes, to those associated with a more generic high risk label. In order to meet this need, an additional section was added to the programme that was aimed at communicating the meaning of risk and risk status. Modifications to the PREPARE programme were undertaken following an established cyclic process that involved training a pool of educators and then piloting the programme to a reprehensive patient group whereupon patient and educator level feedback were collected and the programme revised accordingly. This process was repeated twice.

Table 1 provides an overview of the programme content and structure.

**Table 1 T1:** Outline of the Walking Away programme

**Module**	**Main aims**	**Example activity**	**Theoretical underpinning**	**Time weighting**
Introduction	Welcome/housekeeping			5 minutes
Patient Story	·Give participants a chance to share their knowledge and perceptions of being identified as ‘at risk’ of type 2 diabetes and highlight any concerns they may want the programme to address.	·Participants are asked to share their story, how they were diagnosed as being ‘at risk’ of developing type 2 diabetes and their current knowledge of being ‘at risk’	·Common Sense Model [27]	25minutes
Professional story	Use simple non-technical language, analogies, visual aids and open questions to provide participants with:	·Individuals are helped to plot their individual risk (fasting and 2 hour blood glucose levels, cholesterol and blood pressure levels - assessed at baseline)	·Common Sense Model [27]	35 minutes
			·Dual Process Theory [32]	
	·An overview of healthy glucose metabolism			
			·Social Cognitive Theory [30]	
	·The aetiology of diabetes			
	·An overview of the macrovascular complications associated with being ‘at risk’ of type 2 diabetes.			
Risk story	·The meaning and assessment of risk in the context of developing type 2 diabetes	·Participants are supported to plot their own risk factors onto a risk chart to work out their individual risk areas.	·Dual Process Theory [32]	25 minutes
			·Social Cognitive Theory [30]	
	·Explore personal risk of developing type 2 diabetes			
Break	Refreshments and informal discussion			10 minutes
Physical activity	Use simple non-technical language, analogies, visual aids and open questions to help participants:	·Individuals are helped to plot their individual steps per day scores (assessed at baseline)	·Social Cognitive Theory [30]	55 minutes
			·Implementation Intentions [31]	
	·Identify how physical activity improves glucose control;			
	·Understand the current physical activity recommendations	·Participants are provided with a physical activity diary and encouraged to set their first action plan.		
	·Explore options for incorporating physical activity (primarily walking) into everyday life			
	·Identify barriers to exercise			
	·Form action plans			
	·Use their provided physical activity diaries			
	·Set personal goals (based on baseline pedometer counts)			
			·Dual Process Theory [32]	
Diet	·Give participants an accurate understanding of the link between dietary macro-nutrients and metabolic dysfunction	·Participants are asked to group models of fats and oils into saturated, polyunsaturated and monounsaturated categories.	·Social Cognitive Theory [30]	20 minutes
			·Dual Process Theory [32]	
Conclusion	Questions and future care	Sign-post to locally available groups/programmes		5 minutes

#### Educator recruitment, training and quality assurance

A pool of around 10 educators will be recruited from primary and secondary care and the community. Those recruited from a health care setting will be registered health care professionals and those from the community will be required to process a degree in a health science or be employed within a relevant vocation (i.e. gym instructor). Educator training will consist of two full core days followed by regular ongoing support. Training will be provided through fully accredited national trainers for structured education programmes hosted by the DESMOND collaborative. In order to ensure that the programme philosophy and content are adhered to, a quality assurance procedure was also developed based on established criteria used within the DESMOND programme [34]. This involves an assessor sitting quietly and unobtrusively at the back of the room, with a CD playing into a headphone whilst observing the programme. The CD is silent, except for a beep sounding every 10 s. When the beep sounds, the assessor indicates on a response sheet who is talking at that point (educator or participant), with other activity classed as ‘miscellaneous’ (silence, laughter or multiple conversations during learning activities) [34]. At the same time the assessor fills in a prompt sheet indicating whether or not key learning points within each module were covered. All quality-assured educators receive feedback from their assessor and key goals and action plans are developed in order to help the educator improve their performance.

#### Follow-up support

After the participant’s annual clinical measurement session, all individuals in the intervention group will be invited to attend annual group-based sessions at 12 and 24 months in order to establish the impact of minimal maintenance support on long-term outcomes. These follow-up programmes will be designed to help participants interpret and analyse their annual biochemical and anthropometric follow-up data, review progress and goals and respond to issues, queries and barriers; the main objectives of the programme will also be reinforced. Each follow-up programme will last 2–3 h and will be conducted by a trained educator. All participants will also receive telephone contact between annual sessions in order help participants maintain their motivation.

### Primary outcome

#### Physical activity

The primary end point will be ambulatory activity assessed by tri-axial accelerometers (GT3X, Actigraph, FL, USA). This outcome reflects the overall aim of the intervention and is consistent with the fact that walking activity is the preferred choice of activity within the population. Participants are asked to wear the accelerometer, fitted on their trunks (placed on right anterior axillary line) with a waistband, for seven consecutive days during waking hours. These accelerometers are one of the most extensively validated and accurate on the market and are the only commercially available accelerometers to correlate with energy expenditure as measured by double-labelled water [35].

Overall physical activity as defined by total body movement (counts per day), and time in sedentary, light-, moderate- and vigorous-intensity physical activity will also be assessed by accelerometer and determined by validated counts-per-minute cut-points [36].

Self-reported physical activity will also be measured using the short last-seven-days self-administered format of the International Physical Activity Questionnaire (IPAQ). This questionnaire provides a comprehensive measure of walking and other moderate- to vigorous-intensity activities carried out for more than 10 continuous minutes at work, in the home, as transport and during leisure time. IPAQ has been shown to have reasonable validity compared to accelerometer data (ρ ~ 0.4) and test-retest reliability (ρ ~ 0.7) in the United Kingdom when used as a measure of total moderate- to vigorous-intensity physical activity [37]. For this study, IPAQ will be used to measure total walking activity as well as an overall measure of moderate- to vigorous-intensity physical activity accumulated over all contexts.

All physical activity outcomes will be measured at baseline and 12, 24 and 36 months.

### Secondary outcomes

#### Biochemical variables

This study will measure relevant markers of metabolic and renal health including fasting and 2-h post challenge glucose, HbA1c, lipid profile, liver function tests (albumin, total bilirubin, alkaline phosphatase [ALP], alanine transaminase [ALT]), urea and electrolytes (sodium, potassium, creatinine). Analysis is conducted in the same laboratory located within Leicester Royal Infirmary, UK, using stable methodology standardized to external quality assurance reference values.

Participants will be invited to attend each clinical measurement session after a 12-h fast and 24 h of avoiding vigorous intensity exercise. In concordance with WHO recommendations, those who have a fasting or 2-h blood glucose level in the diabetes range at any clinical measurement session will be called back for a confirmatory oral glucose tolerance test [38].

All venepuncture and OGTT timings will be undertaken by trained phlebotomists who are not part of the scientific advisory team for this study and who are blinded to treatment allocation. All biochemical analysis will also be conducted blinded to treatment group.

#### Anthropometric and demographic variables

Arterial blood pressure will be measured in the sitting position (Omron, Healthcare, Henfield, UK); three measurements will be obtained and the average of the last two measurements will be used. Body weight and body fat percentage (Tanita TBE 611, Tanita, West Drayton, UK), waist circumference (midpoint between the lower costal margin and iliac crest) and height will also be measured, to the nearest 0.1 kg, 0.5% and 0.5 cm respectively. Information on current smoking status, medication history, and ethnicity is obtained by self-report. Social deprivation will be determined by assigning an Index of Multiple Deprivation (IMD) score to participant postcodes [39]. IMD scores are publicly available continuous measures of compound social and material deprivation which are calculated using a variety of data including current income, employment, health, education, and housing.

#### Diet

Diet will be measured using the Dietary Instrument for Nutrition Education (DINE) food frequency questionnaire, which was designed as a method of measuring fibre, fat and unsaturated fat intake in primary care [40]. The DINE food frequency questionnaire has been shown to have reasonable validity when assessed against food records (0.45 < r < 0.51) [40,41].

#### Health related quality of life

Health related quality of life will be measured by the 15D instrument, which can be used as a profile or a single index score utility measure [42]. It consists of 15 dimensions: mobility, vision, hearing, breathing, sleeping, eating, speech, elimination, usual activities, mental function, discomfort and symptoms, depression, distress, vitality and sexual activity. Each dimension is divided into five ordinal levels, by which more or less of the attribute can be distinguished. The valuation system of the 15D is based on an application of the multi-attribute utility theory. A difference of ≥0.03 in the 15D single index score utility score is considered clinically important [42].

#### Perceptions and perceived knowledge of diabetes risk

Perceptions and perceived knowledge of diabetes risk will be measured with the validated brief illness perceptions questionnaire [43]. This eight item instrument uses an 11 point Likert scale (0 = no effect, 10 = complete effect) to measure five cognitive illness representations (consequences, timeline, personal control, treatment control, and identity), two emotional representations (concern and emotion) and illness comprehensibility (perceived knowledge). The brief illness perception question provides a practical and comprehensive measurement of determinants identified in Leventhal’s common sense model [27], one of the key theoretical models underpinning the content and structure of the education programme.

#### Depression and anxiety

Depression and anxiety will be measured with the Hospital Anxiety and Depression Scale (HADS) [44]. HADS consists of 14 items, with two sub-scales measuring symptoms of depression and symptoms of anxiety. HADS is widely used and has been shown to perform well in primary care [45].

### Data analysis

The study will be reported according to the internationally recognised CONSORT statement for the reporting of cluster randomised control trials [16]. Those withdrawn from the study due to a diagnosis of type 2 diabetes will have their last observation carried forward. Sensitivity analysis, using multiple imputation, will be used to assess the effect of those missing to follow-up. Random effects regression models, controlled for baseline value and taking into account cluster, will be used to look at the difference between groups in change from baseline in continuous outcome measures after checking for normality and applying transformation techniques where necessary. Extreme outliers (more than 4 standard deviations from the mean) will be removed from the analysis. Survival curves will be calculated to estimate the cumulative incidence of diabetes. The difference in incidence of diabetes in the groups will be tested using the two-sided log-rank test. Statistical significance will be assessed at the 5% level and all analysis will be 2-sided.

Interim analysis will be conducted and reported at 12 months.

In concordance with other physical activity randomised controlled trials undertaken by our group and others [46,47], we will undertake pooled analysis of the study cohort to determine, through regression analysis techniques, the extent to which change in physical activity is associated with change in key biochemical and anthropometric variables; this will help provide additional information quantifying the strength of the association between physical activity and metabolic health in a population with a high risk of type 2 diabetes; any such analysis will be reported with the caveats inherent in undertaking additional pooled cohort analysis within the context of a randomised controlled trial.

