### Primary objective

· To investigate whether a lifestyle intervention programme, based on a brief pragmatic education programme with minimal ongoing support, can promote sustained long-term increases in physical activity in those identified with a high risk of type 2 diabetes in a primary health care setting.

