Based on a typical GP practice of 4500 adults without known type 2 diabetes, 450 will be eligible for inclusion into the study based on the risk score. Of these we anticipated that 330 (75%) will meet the initial inclusion criteria and be invited to take part in the study. Around 100 (30%) are then expected to consent to take part, of which 10 (10%) will have screen detected type 2 diabetes and therefore excluded at baseline; therefore we anticipate the average cluster size to be 90 individuals (see sample size calculation).

Those diagnosed with diabetes over the course of the study will be informed of their diagnosis and referred back to their health care team for standard care. Progression to type 2 diabetes will be included as a secondary outcome.

Figure 1 shows the flow of the participants through the study.

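### LOCF for participants withdrawn on a diabetes diagnosis covers every outcome, including steps at 24 and 36 months, and no stated sensitivity analysis clearly covers them

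*Protocol article*

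**What the plan says.** Under Data analysis, the protocol article fixes the handling of diagnosed participants: "Those withdrawn from the study due to a diagnosis of type 2 diabetes will have their last observation carried forward". No outcome is exempted. The next sentence reads: "Sensitivity analysis, using multiple imputation, will be used to assess the effect of those missing to follow-up". It does not say whether participants withdrawn for diabetes belong to that group, or whether their carried values would be set to missing and imputed.

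Under Participants: "Those diagnosed with diabetes over the course of the study will be informed of their diagnosis and referred back to their health care team". The purpose of that referral is usual treatment. The section also states: "Progression to type 2 diabetes will be included as a secondary outcome". It does not itself say that measurement stops. The withdrawal is implied only by the Data analysis sentence.

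The primary outcome is steps: "The primary end point will be ambulatory activity assessed by tri-axial accelerometers", measured at baseline and at 12, 24 and 36 months. The primary objective asks whether the programme "can promote sustained long-term increases in physical activity in those identified with a high risk of type 2 diabetes". Diabetes incidence is analysed separately: "The difference in incidence of diabetes in the groups will be tested using the two-sided log-rank test".

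**The concern.** The event that triggers the carrying forward occurs after randomisation and is itself a trial outcome. If the programme changes progression, the share of carried values differs between arms.

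Last observation carried forward (LOCF) assumes no change after the last visit. In a trial of whether an increase in activity is sustained, that assumption is close to the question being asked. A participant diagnosed at 12 months supplies the 12-month step count again at 24 and at 36 months. If activity drifts in either direction after that visit, the analysis cannot see it in these participants.

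The carried value enters the random-effects model as if measured, with no allowance for its uncertainty. For steps there is no evident reason for special handling, because an accelerometer can still be worn after diagnosis. For glucose and HbA1c there is a reason: standard care alters later values.

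**Working it through.** **Yardsticks in the plan.** The plan gives no figure for this rule. Its targets are 2000 steps/day (SD 4000, 90% power) and 0.8 mmol/l for 2-h glucose. The stated minimum of 8 clusters reproduces: 85 per arm × design effect (1 + 89 × 0.02 = 2.78) = 236.3, and 236.3/90 = 2.63 clusters per arm. Adding one cluster per arm for small numbers gives 3.63, rounded up to 4 per arm, or 8 in all. The point made here does not alter that figure.

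**Inputs.** Per arm: 5 practices × 90 = 450 (Abstract, Sample size). Assumed, because the documents give no values: three-year progression P of 5-15%, constant hazard, diagnosis at the 12, 24 or 36-month visit, and a gap g between the carried value and the value that would have been observed.

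**Who carries a value.** Someone diagnosed at the 36-month visit has an observed 36-month value. Only those diagnosed by 24 months carry one to 36 months, and only those diagnosed by 12 months carry one to 24 months:

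- f36 = 1 − (1 − P)^(2/3)
- f24 = 1 − (1 − P)^(1/3)

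| P | f24 | n of 450 | f36 | n of 450 |
|---|---|---|---|---|
| 5% | 1.7% | 8 | 3.4% | 15 |
| 15% | 5.3% | 24 | 10.3% | 46 |

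**Bias at 36 months.** For intervention minus control, bias = f_I × g_I − f_C × g_C. With the same gap in both arms, its size is (f_C − f_I) × |g|.

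- 10% v 6%: f36 = 6.78% and 4.04%, difference 2.74 points.
- 15% v 9%: f36 = 10.27% and 6.09%, difference 4.17 points.

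| Progression, control v intervention | Steps, gap 1000/day | 2-h glucose, gap 1-3 mmol/l |
|---|---|---|
| 10% v 6% | 27 | 0.03-0.08 |
| 15% v 9% | 42 | 0.04-0.13 |

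As a share of the targets: 27/2000 to 42/2000 = 1.4-2.1% for steps, and at most 0.125/0.8 = 16% for 2-h glucose.

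**Direction.** Suppose fewer progress in the intervention arm and the gap is equal. If the carried step counts are too high, the control arm is flattered more and the bias runs against the intervention. If they are too low, it runs in favour. If incidence and gap are both equal across arms, the bias is zero.

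**Unequal staleness.** Suppose incidence is equal but the carried values are 2000 steps/day too high in the intervention arm only. At 2% annual progression the bias is (1 − 0.98²) × 2000 = 0.0396 × 2000 = 79 steps/day. At 10% it is (1 − 0.90²) × 2000 = 0.19 × 2000 = 380 steps/day, in favour of the intervention. This is an extreme case, and nothing in the documents supports or excludes it.

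**The case against.** The case for leaving the rule alone has several parts.

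- **A sensitivity analysis exists.** A reader might infer that LOCF goes untested. The text does not establish this. Multiple imputation is named in the very next sentence, and its coverage of diagnosed participants is unstated, not excluded. Exclusion is the likelier reading, since this group is named separately and already has a filled value. The scope of imputation may also be set out in an analysis plan that is not shown. What stands is that the protocol does not commit to covering them.
- **Diabetes is not failure on the primary outcome.** A reader might infer that the carried values belong to exactly those who failed. That fits glycaemia but not steps, and progression is a secondary outcome.
- **For glucose, the failure stays in the data.** Someone diagnosed at a study visit carries the diabetic-range value, not a later value altered by standard care. This is a fair defence for glucose and HbA1c, and the fix allows for it. It does not extend to steps.
- **The count is easily inflated.** Treating all who progress over three years as carrying a value gives 5-15% of 450, or about 22-68 per arm. That includes those diagnosed at the 36-month visit, whose values are observed.
- **Baseline carried forward.** A reader might suppose that some participants are diagnosed by their own practice before 12 months and so contribute zero change. The protocol describes diagnosis through its own measurement sessions and sets out no such route.
- **Steps are little affected in the moderate cases.** This is correct. It limits the severity of the point but does not justify the rule.

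That carried values are treated as known is a property of the method. The effect on standard errors was not calculated, and no size is claimed for it.

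**Conclusion.** The point holds in a limited form. LOCF is a stated rule for all outcomes, not a detail left open. It is triggered by an event that the intervention is meant to influence, and it puts earlier values into a comparison meant to show sustained change. The protocol does not say that its imputation analysis covers the group.

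On the assumed rates, about 15-46 of 450 per arm would carry a value to 36 months. The bias would be about 27-42 steps/day and 0.03-0.13 mmol/l in 2-h glucose. These figures rest wholly on assumed progression and gaps, and larger bias requires staleness that differs between arms. The documents do not support a claim that the rule favours the intervention, because the direction cannot be known and the bias may be zero. The log-rank comparison of diabetes incidence does not use carried values and is untouched. The rule should be changed, but it does not by itself undermine the trial.

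**What to change.** 1. **Steps and other non-glycaemic outcomes.** Replace LOCF in the main analysis with a repeated-measures mixed model over 12, 24 and 36 months with a practice effect, or with multiple imputation that includes practice, arm and diabetes status. Keep LOCF only as a sensitivity analysis.
2. **Glucose and HbA1c.** The carried diagnostic value may stay as the main analysis. State explicitly that multiple imputation is extended to diagnosed participants as a sensitivity analysis.
3. **Follow-up.** Where feasible, keep diagnosed participants who agree in the accelerometer, anthropometric and questionnaire follow-up that is already scheduled. Without any data after diagnosis, both the mixed model and the imputation rest on assumptions that cannot be checked.

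The cost of items 1 and 2 is revised analysis wording and a little more analysis work. Item 3 is a modest change to follow-up for a small number of participants. It goes beyond analysis wording, because recruitment began in 2010. It concerns measurement only and leaves clinical care as the protocol has it.
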